### Informed Consent

The Research Ethics Board (REB) at WCH and the University of Toronto will review the project proposal. Amendments will be made to appease both boards.

Ethical Considerations

Anonymity and confidentiality of potential and actual participants will be ensured throughout the investigation using standard procedures in place at the WCH and the University of Toronto. All consent forms, questionnaires, data files on disks, and field notes will be stored in a locked file that will be accessed only by the investigators. No identifying information will be stored in the analytic datasets. Participants will be identified only by a study number.

### Privacy

#### Smartphone Transmissions

Patient data collected using the mobile app was double encrypted on the server and the phone. All patients will be informed how to password protect their phone. Designed from the ground up to ensure security and privacy, the app conforms to leading health care audit and interoperability standards including Personal Health Information Protection Act (PHIPA), Health Level Seven International (HL7), Information Technology Infrastructure Library (ITIL), and Statement on Auditing Standards 70 (SAS70). Multiple layers of encryption, including resting state Advanced Encryption Standard (AES) encryption, in transmission content encryption using unique per patient public / private key pairs, and in transmission Transport Layer Security / Secure Sockets Layer (TLS/SSL) protocol encryption were applied to maintain the highest level of patient confidentiality as possible. Modern infrastructure design leveraging distributed infrastructure as a service (IaaS) and software as a service (SaaS) cloud computing services for seamless accessibility, redundancy, and scalability were also utilized.

#### Research Study Data Storage

Access is restricted to the locked filing cabinets in the investigator’s office, no identifiers will be included on data sheets (only identification numbers will be used), and password-protected databases will be used. Data will be stored on a password-protected, double-encrypted, secure server. Any data stored on a mobile device (eg, universal serial bus [USB] key) will be encrypted as per WCH policies. All de-identified data will be stored for 5 years past publication and will be destroyed by shredding. The physicians will keep patient charts for the standard time period.

### Risks

There are no major identified risks from participation in this study. The “risks” of using a mobile phone or tablet device are (1) the timing of diagnosis of a complication since there is a 4% risk of complication following surgery [15], and participating in mobile versus in-person follow-up care may have an impact on the timing of diagnosis of complication; (2) security issues due the risk that someone could steal and possibly break into the contents of the phone; however, the mobile phones used in this study are double encrypted and password protected, and information is transmitted in accordance with Canadian’s Personal Information Protection and Electronic Documents Act; (3) the risk of injury from dropping the mobile phone on a foot or surgical wound, using the mobile phone while driving or operating machinery, distraction during other tasks, mobile phone overuse syndrome, and repetitive strain injury; however, the time required for the response is approximately 5 minutes; and (4) anxiety arising through possible complications from surgery, or possible loss of or damage to the device.

### Perceived Undue Influence

Patients will be generally informed about the study by their surgeon (JS or MB). The study coordinator and researcher (KA) will be responsible for the formal study explanation and informed consent process. These two people are in no way involved in the direct care of patients. All patients will be informed that their care will be in no way compromised if they choose not to participate. All patients will be informed of their ability to leave the study at any time.

### Recruitment Procedures

All patients presenting for breast reconstruction will be screened for inclusion in the study. We will consecutively approach patients to participate in the study. A member of the health care team will inform patients about the study prior to surgery. If interested in participating, a study coordinator or researcher (KA) will introduce the patient to the technology so that they can better judge what is required of them. This will include introduction to the QoR-9 and VAS score on the mobile app (see Multimedia Appendix 2). The patients will be assured of their ongoing surgical care regardless of their participation. Patients who agree to participate will review and sign the appropriate consent form. They will have the opportunity to discuss the study with the attending surgeon. Written consent will be obtained for all prospective patients. After the patient has consented to the trial, they will be randomized to the mobile app or in-person follow-up arm using the program ralloc in Stata statistical software [20].

The mobile app follow-up care stream will receive an instruction sheet detailing how to use the app. The patient will receive training on how to use the app from the study coordinator or researcher (KA). The patient will be given a mobile phone on the day of surgery and will review the use of the mobile app again at this time. This will also help the patient judge what is required of them and serve as an opt-out point.

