### Sample Size

The average breast reconstruction patient attends two in-person follow-up visits within the first month after surgery. If we assume that we can avert at least one in-person visit in the mobile app arm and that we have equal number of participants in both groups, we can use the E-test for count data to generate a sample size of 64 (32 patients per group) at a power of 95% (*P*=.05). The E-test is more robust and more powerful than the Conditional test (C-test) originally described to compare two counts. If we assume a 10% dropout rate, we will increase our sample size target to 36 patients per group.

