### Timeline

Any given patient may be recruited for the study up to 2 months prior to their surgery date. They will participate in the study for a total of 1 month following their surgery. Set-up and REB approval (1-2 months); a concurrent enrollment and data collection period to attain the required study participants (4-5 months); merging, cleaning, and debugging (1 month); and development of value messages for decision-makers and knowledge dissemination activities (2 months). This study will require approximately 1 year for completion. Its precise duration depends on the patient enrollment rate.

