### Handling Missing Data

We will generate “best” and “worst” case scenarios for the missing data to determine if there is any change in findings.

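### After randomisation, only the app arm gets an explicit day-of-surgery opt-out, so app-averse patients can be lost selectively from one arm

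*Protocol article*

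**What the plan says.** All places are in the protocol article.

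- **Order of events.** Recruitment Procedures: "After the patient has consented to the trial, they will be randomized to the mobile app or in-person follow-up arm". Under Allocation Concealment the participant opens the envelope herself, and the trial is open, so she knows her arm from that moment.
- **Time gap.** Timeline: "Any given patient may be recruited for the study up to 2 months prior to their surgery date".
- **What the app arm then receives.** The next paragraph of Recruitment Procedures begins: "The mobile app follow-up care stream will receive an instruction sheet detailing how to use the app". It goes on to training, a phone on the day of surgery and a further review of the app, and ends: "This will also help the patient judge what is required of them and serve as an opt-out point". No matching step is described for the in-person arm.
- **General right to withdraw, both arms.** Perceived Undue Influence: "All patients will be informed of their ability to leave the study at any time".
- **How the primary outcome is obtained.** Under Measuring Outcome Variables, the coordinator collects the visit count by telephone at 4 weeks. Data Collection Overview plans four attempts to reach every patient.
- **Missing data.** Best and worst "case scenarios for the missing data to determine if there is any change in findings". No values are given.

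**The concern.** The right to leave is the same in both arms, but the prompt to use it is not. Only app patients are asked to think again, at a fixed moment, knowing their allocation and having seen what the app demands. Those who step out there are likely to be the patients least willing to be followed remotely, and so the most likely to want visits. Their counterparts in the in-person arm stay in.

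The text leaves open whether opting out means handing back the phone or leaving the trial. On the first reading the week-4 interview can still be done and randomisation is preserved. On the second there is no primary outcome, the groups are no longer those formed by randomisation, and the app arm's visit count looks lower than it would for everyone assigned to the app.

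**Working it through.** **Inputs from the document (Sample Size).** Control mean 2 visits: "The average breast reconstruction patient attends two in-person follow-up visits within the first month after surgery". One visit averted, so app mean 1. E-test, 95% power, P=.05, 32 per group; 10% dropout, raised to 36 per group.

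**1. The plan's own figure.** Exact E-test power for 2 versus 1 at 32 per arm is 95.2% one-sided and 91.1% two-sided, so the stated 32 reproduces as a one-sided calculation. Dropout: 32 / (1 − 0.10) = 35.6, rounded up to 36, as stated. That allows for 36 − 32 = 4 lost per arm.

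**2. Effect of losing opt-outs from the app arm.** Assumptions, not in the documents: a fraction f of the app arm opts out, f = 10–20%; these patients average 2 visits; the remaining app patients average 1; the control mean is 2.

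All-randomised app mean = (1 − f) × 1 + f × 2 = 1 + f.

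| f | App mean, all randomised | Visits averted, all randomised | Visits averted, opt-outs excluded |
|---|---|---|---|
| 10% | 1.1 | 2 − 1.1 = 0.9 | 2 − 1.0 = 1.0 |
| 20% | 1.2 | 2 − 1.2 = 0.8 | 2 − 1.0 = 1.0 |

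Exclusion overstates the averted visits by f, that is by 0.1 to 0.2 visits.

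**3. Power if opt-outs are kept as randomised.** Two-sided exact E-test with 36 analysed per arm: 93.9% for 2 versus 1.0, 87.1% for 2 versus 1.1, 76.8% for 2 versus 1.2. Because 36 already includes the dropout allowance, these figures assume that every patient has an outcome.

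**4. Secondary check: can the best/worst-case rule absorb the loss?** Take 4 of 36 missing per arm, with the 32 completers exactly at plan (app total 32, control total 64). Give each missing app patient a visits and each missing control 0. Then T = 32 + 4a, C = 64, RR = T/C, and z = ln(C/T) / √(1/T + 1/C).

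| a / control value | T | RR | Two-sided p |
|---|---|---|---|
| 2 / 0 | 40 | 0.63 | 0.020 |
| 3 / 0 | 44 | 0.69 | 0.056 |
| 4 / 0 | 48 | 0.75 | 0.13 |
| 5 / 0 | 52 | 0.81 | 0.27 |

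If the loss falls on the app arm alone, say 7 of 36 (19%) with a complete control total of 72, then T = 29 + 7a. This gives p = 0.0075 at a = 2, 0.048 at a = 3 and 0.19 at a = 4.

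**The case against.** The case on the other side has real substance.

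- **Withdrawal is open to both arms**, and moving the opt-out cannot remove it. That is true, but a general right is not the same as a scheduled prompt given to one arm.
- **Much app aversion is screened out before allocation.** Patients must be able to use a mobile device, and the technology is shown before consent. This should make later opt-outs fewer. It also shows that the day-of-surgery decision point is largely redundant.
- **The outcome does not depend on the app.** A patient who declines the phone can still be interviewed. This stands, provided that opting out means only that, and the text does not say so.
- **The article condenses a fuller protocol**, so the absence of an intention-to-treat statement or of imputation detail is not a fault here. I accept that. The point rests on what Recruitment Procedures does state.
- **The power figures do not measure the harm.** Correct. They describe the trial with opt-outs retained, which is the cost of the remedy.

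A reader might also infer that the best/worst-case rule would make the planned result non-significant at the planned dropout. The document does not support that. It assigns no values, and it presents the scenarios as a check on the findings, not as the main analysis. At 2 visits for lost app patients and 0 for lost controls, the planned effect stays significant. Losing significance depends on values that the reader has to supply.

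**Conclusion.** The point holds for the opt-out. The plan places an explicit decision point after allocation, on the day of surgery and in one arm only, and does not say what opting out entails. Followed as written, it invites loss related to arm.

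Under the assumed 10–20% opt-out with 2 visits each, excluding these patients reports 1.0 visit averted where the all-randomised figure is 0.9–0.8. The rate and the visit count are illustrations. In this illustration the 1.0 is the effect among patients willing to use the app, which is not the effect of offering it to everyone randomised. If app-averse patients also make more visits than average under usual follow-up, the bias would be larger.

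The document does not show that opt-outs would in fact be dropped from the analysis. It leaves that possibility open.

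The missing-data rule is a secondary matter. Worst case is undefined for a visit count that has no upper limit. With 4 lost per arm the result survives at 2/0, is borderline at 3/0 and is lost at 4/0. The check can change the finding but need not.

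**What to change.** 1. Place the opt-out decision before the allocation envelope is opened. The introduction to the technology already precedes consent and serves the same purpose.
2. State that refusal after allocation means declining the device and not leaving the study. Keep such patients in the app arm as randomised and carry out the same week-4 interview. The right to withdraw fully stays as it is for both arms.
3. As a minor addition, state in advance the visit values that define the best and worst cases, or show the range over which the conclusion changes.

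The cost is a reordering of existing steps and a few sentences. The real downside is dilution by non-users: under the assumption used above, two-sided E-test power at 36 analysed per arm is about 87–77% instead of 94%. The diluted effect is the one that a trial described as pragmatic sets out to estimate.

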### Data Collection Overview

The QoR and VAS pain scores will be collected from all patients at 4 weeks after surgery (see Figure 1). The in-person study group will perform this via telephone interview, and the mobile app group will perform this via mobile app. Our study coordination or researchers (KA) will collect all telephone questionnaires at 4 weeks after surgery. These persons will administer the questionnaire capturing email, telephone and in-person encounters, postoperative complications (Multimedia Appendix 3), and the cost survey (Multimedia Appendix 4). They will also administer the post-pilot survey capturing patient satisfaction (Multimedia Appendix 1) at 4 weeks after surgery. The study coordinator or researcher (KA) will attempt to contact every patient four times over the 4^th^ week after surgery.

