### Intervention

Eligible patients will be randomized in equal proportions (1:1) between mobile app and in-person follow-up care. All patients will receive what is currently the medical standard of care in this hospital. Patients in the conventional follow-up group will have a planned clinic follow-up at 4 weeks postoperative. This is the follow-up schedule currently used by both surgeons. At these scheduled follow-ups, patients will be asked to complete the VAS to assess pain and the QoR-9.

The mobile app follow-up group will have no planned in-person follow-up at 1 week and 4 weeks postoperative. However, these visits will be replaced with surgical site examination via submitted photos, VAS, and QoR-9 questionnaire monitoring. All of this information is submitted via the mobile app (QoC Health Inc, Toronto). Patient reporting will begin following discharge from the recovery room. Since 75% of complications occur within the first 2 weeks of discharge [21], we will use daily monitoring for 2 weeks and then weekly monitoring for 4 weeks. The data entered through the mobile phone app will reach a double-encrypted server. The surgeon will then use a wireless interface to access that data and monitor the patient’s condition (not in real time). High pain scores will be flagged in the database for quick viewing. Any red flags will prompt in-person follow-up. Physicians will summarize the clinical findings recorded by the mobile app at 1 week and 4 weeks postoperative using the prototypical subjective, objective, assessment, and plan (SOAP) note.

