A societal perspective will be adopted wherein all costs are assessed irrespective of the payer [22]. This perspective was chosen based on the US Panel on Cost-Effectiveness in Health and Medicine recommendations. This recommendation is meant to improve comparability and consistency across studies [23]. Furthermore, while a broad societal perspective will be adopted, results will also be presented using a narrower health system perspective that may be of key interest to health administrators and policy decision makers. This alternative perspective focuses on costs borne within the health system and excludes external costs as well as costs borne by patients and their caregivers.

Currently, there are no validated questionnaires that capture patient satisfaction with postoperative care. We have created a post-pilot survey that captures patient satisfaction with the care and information received. All answers are recorded using a 5-point Likert scale (Multimedia Appendix 1). We will also use the QoR-9 scores and VAS recorded at 4 weeks postoperative. Psychometric properties of the QoR-9 include convergent validity and discriminant construct validity. There is also good interrater agreement and internal consistency [24]. The test-retest reliability was 0.61 (*P*<.001). The preferred cut-off is 0.7; however, the QoR-9 was still favored over the QoR-40 due to its ease of use (<2 minutes required to complete the survey) [24].

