### Measuring Outcome Variables

#### Primary Outcome

The total number of physician visits (including specialist, family physician, and emergency department) related to the surgery will be captured at 4 weeks after surgery by the study coordinator over telephone (see Multimedia Appendix 3).

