Patient satisfaction will be measured at 4 weeks after surgery using the post-pilot survey (Multimedia Appendix 1). The study coordinator will administer this over the telephone. The QoR-9 scores will be recorded at 4 weeks after surgery using the mobile app at home or a tablet during a scheduled clinic visit, depending on the patient’s study arm.

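### Week-4 QoR-9 and pain VAS are collected by a different mode or setting in each arm, and the protocol contradicts itself on whether controls answer by telephone or in clinic

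*Protocol article*

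**What the plan says.** All places are in the Protocol article.

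- **Data Collection Overview:** QoR and VAS are collected from all patients at 4 weeks, split by arm: "The in-person study group will perform this via telephone interview, and the mobile app group will perform this via mobile app".
- **Intervention:** for the conventional arm's planned clinic follow-up, "At these scheduled follow-ups, patients will be asked to complete the VAS to assess pain and the QoR-9". No medium is named. For the app arm's photos, VAS and QoR-9, "All of this information is submitted via the mobile app (QoC Health Inc, Toronto").
- **Secondary Outcomes, under Measuring Outcome Variables:** the week-4 QoR-9 is recorded "using the mobile app at home or a tablet during a scheduled clinic visit", depending on study arm. The VAS is not mentioned.
- **Secondary Outcomes, the earlier section of that name:** next to the satisfaction survey, "We will also use the QoR-9 scores and VAS recorded at 4 weeks postoperative". This is what makes the two scores secondary outcomes.
- **Primary Outcome, under Measuring Outcome Variables:** the visit count "will be captured at 4 weeks after surgery by the study coordinator over telephone", with no split by arm.

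**The concern.** There are two linked problems.

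First, the instructions for the control arm conflict. One section says telephone and two say clinic visit. Each is a positive instruction, so this is not an effect of condensing a longer document. Staff could follow either instruction, or use both for different control patients.

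Second, resolving the conflict does not by itself make the arms comparable. App patients always self-complete in the app, and no version has controls answering in the same way and place. Mode or setting is thus the same variable as arm, and no covariate adjustment can separate them. A difference in reported recovery or pain could come from how the question was put, and a mode effect in the opposite direction could hide a real difference.

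The protocol gives these scores weight. Under Selection Criteria it excludes patients with chronic pain, regular narcotic use or relevant allergies in order to protect the reliability of the pain ratings.

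**Working it through.** **Step 1: set the sections side by side.**

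| Section | Control arm | App arm | Scores covered |
|---|---|---|---|
| Data Collection Overview | telephone interview | mobile app | QoR and VAS |
| Intervention | at the scheduled clinic follow-up, medium not named | mobile app | QoR-9 and VAS |
| Secondary Outcomes (Measuring Outcome Variables) | tablet at a scheduled clinic visit | app at home | QoR-9 only |

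For the QoR-9, telephone in one section conflicts with clinic in two. For the VAS, the conflict is between Data Collection Overview and Intervention only. In no row do the two columns match.

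**Step 2: how far the arms differ under each version.**

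- *Telephone version:* an interviewer-administered, spoken response is compared with a self-completed response on a screen. Administration and presentation of the scale both differ.
- *Clinic-tablet version:* both arms enter the QoR-9 electronically. What remains is mainly setting, clinic against home.

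**Step 3: which outcomes are touched.** Only the week-4 QoR-9 and VAS. The visit count, calls and emails, complications, the cost survey and the satisfaction survey are described as collected by telephone without a split by arm.

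**Step 4: illustration of size.** The concern rests on no figure in the plan, and the documents give neither a mode effect nor an SD for either score. The only inputs are the sample sizes:

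- 32 per arm, from Sample Size. This reproduces: an exact E-test for Poisson means of 2 and 1 visits with 32 per arm gives power 0.952 at one-sided 5% (0.911 two-sided, which is a separate matter).
- 36 per arm, also from Sample Size: "If we assume a 10% dropout rate, we will increase our sample size target to 36 patients per group". Check: 32 / (1 − 0.10) = 35.6, rounded up to 36.

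Suppose there is no true difference and the only difference between arms is an assumed mode shift of d SD. With a normal approximation and a two-sided 5% test:

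- non-centrality = d × √(n/2)
- rejection rate = Φ(non-centrality − 1.96) + Φ(−non-centrality − 1.96)

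For n = 32 and d = 0.2, the non-centrality is 0.2 × √16 = 0.8. The rate is Φ(−1.16) + Φ(−2.76) = 12.6%.

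| Assumed shift d | 32 per arm | 36 per arm |
|---|---|---|
| 0 (one common mode) | 5% | 5% |
| 0.1 SD | 6.9% | 7.1% |
| 0.2 SD | 12.6% | 13.6% |
| 0.3 SD | 22.4% | 24.7% |
| 0.5 SD | 51.6% | 56.4% |

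For scale, the difference detectable with 80% power (my choice; the plan does not power on these scores) is (1.96 + 0.84) × √(2/32) = 0.70 SD with 32 per arm. With 36 per arm it is 2.80 × √(2/36) = 0.66 SD.

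**The case against.** The best case on the other side is that little depends on this.

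- The abstract's list of secondary outcomes does not name QoR-9 or VAS; the body adds them beside the satisfaction survey. The Data Analysis Plan names no between-arm test of either score, and nothing is powered on them. This stands, and it limits the consequence. It does not remove it, because scores listed as outcomes of a two-arm trial will be compared by arm.
- If the tablet version governs, both arms enter the QoR-9 on a screen and the mode effect may be small. This also stands. The interviewer argument applies only to the telephone version.
- Figure 1, which Data Collection Overview cites for this procedure, is not shown and may clarify the intent. It could not make the written sections agree.

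A reader might also infer more than the text supports:

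- *Three incompatible modes.* The conflict is two-way. Intervention names no medium, so it is compatible with the tablet.
- *A VAS cannot be given by telephone at all.* The documents do not say so. The response format is in Multimedia Appendix 2, which is not shown, and Recruitment Procedures has patients introduced to the scale on the app before consent. What can be said is that a spoken answer and an on-screen answer are not the same administration.
- *A known share of the detectable difference is artefact.* An assumed shift of 0.2 to 0.5 SD is 0.2/0.70 = 29% to 0.5/0.70 = 71% of the figure for 32 per arm, but the SD range has no source in the documents.
- *The trial's main result is compromised.* It is not: the visit count is captured in the same way in both arms.

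**Conclusion.** The point holds as a measurement problem confined to two secondary scores. The contradiction (telephone against clinic visit for controls) and the alignment of mode or setting with arm are both plain in the text and need no assumption. The alignment is serious if controls are interviewed by telephone and milder if they use a tablet in clinic. Its direction and size cannot be known from the documents. The rejection rates above show only how sensitive a comparison of this size would be to assumed shifts, under a normal approximation with no true difference. The primary outcome, the other telephone-collected outcomes and the sample size are unaffected. It should be corrected before data collection, because analysis cannot repair it afterwards.

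**What to change.** Make Intervention, Data Collection Overview and Secondary Outcomes (Measuring Outcome Variables) state the same procedure for the week-4 QoR-9 and pain score, and use one mode in both arms. Either of these would do:

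1. **Telephone for everyone.** Add the whole QoR-9 and a verbally administered numeric pain score to the week-4 call that the coordinator already plans to every patient. The app arm's own week-4 entries would remain as monitoring and not serve as the outcome. Cost: a few minutes more per call, and a pain item that differs from the app's VAS.
2. **Self-completion at home for everyone.** Use a stand-alone electronic form sent to both arms at the same time point. It should not be the monitored app, since giving controls the app would hand them part of the intervention. Cost: one survey link.

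With a common mode and setting the assumed shift becomes zero, and the two-sided error rate under no true difference returns to 5%. No sample size changes.
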